## Abstract

**Background:**

Extracorporeal membrane oxygenation (ECMO) provides support for the pulmonary or cardiovascular function of children in whom the predicted mortality risk remains very high. The inevitable host inflammatory response and activation of the coagulation cascade due to the extracorporeal circuit contribute to additional morbidity and mortality in these patients. Mixing nitric oxide (NO) into the sweep gas of ECMO circuits may reduce the inflammatory and coagulation cascade activation during ECMO support.

**Objective:**

The purpose of this study is to test the feasibility and safety of mixing NO into the sweep gas of ECMO systems and assess its effect on inflammation and coagulation system activation through a pilot randomized controlled trial.

**Methods:**

The Nitric Oxide on Extracorporeal Membrane Oxygenation in Neonates and Children (NECTAR) trial is an open-label, parallel-group, pilot randomized controlled trial to be conducted at a single center. Fifty patients who require ECMO support will be randomly assigned to receive either NO mixed into the sweep gas of the ECMO system at 20 ppm for the duration of ECMO or standard care (no NO) in a 1:1 ratio, with stratification by support type (veno-venous vs veno-arterial ECMO).

**Results:**

Outcome measures will focus on feasibility (recruitment rate and consent rate, and successful inflammatory marker measurements), the safety of the intervention (oxygenation and carbon dioxide control within defined parameters and methemoglobin levels), and proxy markers of efficacy (assessment of cytokines, chemokines, and coagulation factors to assess the impact of NO on host inflammation and coagulation cascade activation, clotting of ECMO components, including computer tomography scanning of oxygenators for clot assessments), bleeding complications, as well as total blood product use. Survival without ECMO and the length of stay in the pediatric intensive care unit (PICU) are clinically relevant efficacy outcomes. Long-term outcomes include neurodevelopmental assessments (Ages and Stages Questionnaire, Strength and Difficulties Questionnaire, and others) and quality of life (Pediatric Quality of Life Inventory and others) measured at 6 and 12 months post ECMO cannulation. Analyses will be conducted on an intention-to-treat basis.

**Conclusions:**

The NECTAR study investigates the safety and feasibility of NO as a drug intervention during extracorporeal life support and explores its efficacy. The study will investigate whether morbidity and mortality in patients treated with ECMO can be improved with NO. The intervention targets adverse outcomes in patients who are supported by ECMO and who have high expected mortality and morbidity. The study will be one of the largest randomized controlled trials performed among pediatric patients supported by ECMO.

**Trial Registration:**

Australian New Zealand Clinical Trials Registry ACTRN12619001518156; https://www.anzctr.org.au/Trial/Registration/TrialReview.aspx?id=376869

**International Registered Report Identifier (IRRID):**

DERR1-10.2196/43760

## Introduction

Extracorporeal membrane oxygenation (ECMO) has gained widespread acceptance as a rescue treatment for refractory cardiovascular and respiratory failure among neonates, children, and adults [1-3]. While morbidity and mortality in ECMO are predominantly affected by the severity of preexisting disease, the contribution of iatrogenic factors to patient-centered outcomes is becoming increasingly recognized [4]. Despite major improvements in ECMO devices, the exposure of host blood to large artificial organ surfaces, mechanical cell stress, and reperfusion injury result in the activation of the coagulation system and generate a severe inflammatory response [5]. Studies on extracorporeal circuits (including bypass circuits) have shown that hypoxic-ischemic injury and the release of damage-associated molecular patterns trigger an inflammatory cascade closely related to sepsis-induced systemic inflammatory response syndrome. It is characterized by endotoxin release, leukocyte and complement activation, and widespread activation of inflammatory mediators, resulting in endothelial leak, increased oxygen consumption, and organ dysfunction [6]. Both intrinsic factors and extrinsic factors, such as exposure to injured tissue, contribute to excessive inflammation and coagulation system activation and may be further aggravated by cross talk across the complement and coagulation systems [7]. Therefore, it is not surprising that thrombosis and hemorrhage remain among the most common complications seen with ECMO [8].

These ECMO-related side effects expose patients to substantial morbidity and can lead to death or devastating long-term outcomes, even if the primary reason for requiring ECMO has been resolved. Importantly, some pediatric data show that more than 85% of patients who die during or after their ECMO run have developed either bleeding or clotting complications [9].

Nitric oxide (NO) mediates anti-inflammatory host responses and regulates both endothelial functions as well as microvascular inflammation. The mixing of NO into the sweep gas that runs into the oxygenator in neonates and children undergoing cardiopulmonary bypass has been investigated in several pilot studies with promising results, and a large randomized controlled trial (RCT) has recently been published [10-13]. In this trial, the effects of NO used in a bypass circuit for pediatric cardiac surgery were tested [13]. No effect on mortality or on the duration of ventilation was observed, though the safety of NO was high. The treatment duration on cardiopulmonary bypass is a few hours, whereas ECMO support lasts days to weeks, making the 2 clinical scenarios not directly comparable. In addition, mixing NO into the sweep gas (at 30, 50, and 80 ppm) in an animal model of ECMO significantly reduced the host response, with suppression of tumor necrosis factor *α* (TNF-*α*) and interleukin (IL)-6 expression ([name], unpublished data, April 2023). A single-center observational study using historical controls reported the safety and outcomes of NO at 20 ppm mixed into the sweep gas of the ECMO oxygenator. The authors observed a lower blood product administration and a marginal improvement in the survival of patients on NO compared to the historical controls without any NO. There are no randomized studies on the effect of NO mixed into the oxygenator on patients treated with ECMO.

The Nitric Oxide on Extracorporeal Membrane Oxygenation in Neonates and Children (NECTAR) study was designed to investigate in a randomized clinical trial whether mixing NO into the sweep gas in neonates and children treated with ECMO is feasible (recruitment, randomization, and protocol compliance) and safe (accurate NO delivery and methemoglobin levels). Efficacy will be tested by measuring ECMO-free days (the number of days that patients spend alive and free from ECMO is censored at 30 and 90 days) and by assessing the inflammatory host response and coagulation activation. We hereby describe the NECTAR trial protocol.

## Methods

The NECTAR trial is an investigator-initiated, 50-patient, open-label, single-center, pilot RCT with neonates and children who require ECMO support.

### Study Setting

A tertiary pediatric intensive care unit (PICU) in Australia with approximately 30 ECMO runs annually.

### Participants

Eligible children will be identified during the clinical deterioration typically seen prior to ECMO support commencement, such as progressive respiratory, cardiovascular, and cardiorespiratory failure, including cardiopulmonary arrest. If the situation permits, prospective consent will be sought; otherwise, delayed consent or consent to continue the approach will be applied.

### Inclusion Criteria

All infants and children (birth to ≤16 years) that are commenced on ECMO will be eligible for inclusion in the study if there is the ability to obtain prospective consent or consent to continue from parents or guardians. In addition, infants or children that are commenced on ECMO at the colocated Neonatal Intensive Care Unit will be eligible for inclusion in the study. Patients who are commenced on ECMO outside of these units will not be eligible for the study.

### Exclusion Criteria

Neonates and children treated with ECMO who were retrieved to the PICU on ECMO, those with preexisting methemoglobinemia (methemoglobin [MetHb]>3%), and patients managed on a ventricular assist device only without an oxygenator were present in the ECMO circuit.

### Randomization and Blinding

Treatment group allocation will be performed using a web-based REDCap electronic data capture tool hosted by The University of Queensland [14,15]. A randomization sequence using variable block randomization with a 1:1 ratio was uploaded into REDCap prior to the screening of the first patient. Randomization is stratified by veno-arterial (VA) versus veno-venous (VV) support. Where conversion of VV to VA or VA to VV occurs, patients will remain in the initial randomization allocation and strata. When a second ECMO run is commenced, the patient will be randomized again.

### Consent

Prospective consent will be sought from the parents or guardians of any child for whom a decision to be commenced on ECMO has been made. Where possible, this consent will be obtained before the commencement of ECMO. However, due to parental stress and cognitive overload at the time of cannulation, consent can also be obtained following randomization under the consent to continue model (termed “delayed consent” previously) [16]. Prior to or after ECMO commencement, parents will be provided with study information, including printed study flyers and links to web-based study documentation.

### Blinding of the Intervention

Blinding is not possible, as the NO delivery device makes a distinctive noise during standard operation. Further, the NO levels need to be adjusted depending on sweep flow, which requires nurses by the side to identify whether NO is being delivered or not.

### Interventions

Infants and children will be randomly assigned to receive either NO or standard care. Those allocated to the intervention (NO) will receive 20 ppm of NO mixed into the sweep gas running into the oxygenator during their ECMO run. The NO concentration will be maintained at 20 ppm using a NO delivery system (Sokinox, Maquet), or a similar device. Continuous sampling of NO and NO_2_ concentrations is performed by the Sokinox machine by gas aspiration after the NO injection site. Patients allocated to the standard study arm will receive the standard oxygen-air mix in the ECMO oxygenator as per institutional practice and protocol.

### Relevant Concomitant Coagulation Management and Intensive Care Treatment

Apart from mixing NO into the sweep gas flow of the ECMO system, no other patient management parameters will be changed, and institutional practices and protocols will be followed. Methods and goals of anticoagulation will remain unchanged for any other ECMO management and treatments, such as decisions to decannulate, ventilation support, inotrope management, fluid intake, fluid removal practices, or antimicrobial or immunological treatments.

### Safety Data Monitoring

A data and safety monitoring board (DSMB) will monitor the conduct of the study and the accrual of data. The DSMB will consist of a chairperson (experienced in clinical trials), a pediatric intensivist, a cardiac surgeon, and a statistician. The DSMB will be independent of the study investigators and will monitor adverse events in the study as well as ensure the validity and timeliness of the data collection. The DSMB may advise the Chief Investigator to terminate the trial, which would necessitate safety concerns in this step. The DSMB is expected to meet at least 4 times during the study period.

### Monitoring

The study team will be responsible for all documentation of the study nurse’s and the investigator’s training records and credentials. All consent forms will be reviewed by the study team. The perfusion data collection forms will be compared to the source documentation to ensure both the completeness and accuracy of the data. All severe adverse events will be recorded and reported to the local Human Research and Ethics Committee (HREC) as per the institutional guidelines.

### Ethics Approval

This protocol and the informed consent document, and any subsequent modifications, have been reviewed and approved by the human research ethics committee (reference number HREC/18/QCHQ/49018). This study will be conducted in compliance with this version of the protocol. Any change to the protocol document or informed consent document that affects the scientific intent, study design, patient safety, or anything that may affect a participant’s willingness to continue in the study is considered an amendment, and therefore will be written and filed as an amendment to this protocol or the informed consent document. All protocol deviations will be reported to the principal investigator, recorded in REDCap, and reported to HREC. Protocol deviations and violations will be assessed for clarification by the principal investigator. The study was approved by the local HREC (HREC/18/QCHQ/49018) and has been registered with the Australian New Zealand Clinical Trials Registry (ACTRN12619001518156). The NECTAR trial commenced recruitment in August 2020

### Sample Size

The NECTAR trial is a pilot RCT with the main focus on feasibility, safety, and exploration of efficacy. A sample size of 50 patients has been chosen in line with the recommendations for pilot studies that anticipate a medium effect size for a continuous primary outcome for the main trial [17].

### Data Collection, Management, and Analysis

#### Data Collection

Baseline variables (demographics, primary diagnosis, comorbidities including syndromes), precannulation disease severity, precannulation surgery (such as cardiac surgery), cannulation technique, primary and secondary end points, as well as predetermined physiological variables of interest, will be recorded and entered prospectively into a purpose-built REDCap database [14,15]. Treatment that is administered continuously (such as heparin or inotropes) will be recorded as maximal values that were maintained for at least 4 hours. Physiological and blood parameters will be recorded precannulation, at 1, 12, and 24 hours post cannulation, and daily thereafter. The duration of circulatory, renal, and ventilatory support on and off ECMO will be recorded. Gross functional performance assessment will be recorded upon admission to the PICU and upon discharge from the hospital [18].

Participant data confidentiality will be ensured by the study coordinator, the research staff, and the institution sponsoring the trial. All data, as well as the study protocol and any other information that this trial may generate, will be held in strict confidence.

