### Secondary Clinical Outcomes

The secondary clinical outcomes include mortality at 30 and 90 days. ECMO-free and PICU-free survival censored at 30 and 90 days post randomization, length of stay at the hospital post randomization, average daily blood product usage, complement system activation with measurements of complement (C)1q, C5a, C9, C3, C4, complement factor B, complement factor H, and Mannose-binding Lectin, as well as neurodevelopmental function and quality of life at 6 and 12 months, will be considered (Textbox 3).

Subanalyses for the Nitric Oxide on Extracorporeal Membrane Oxygenation in Neonates and Children (NECTAR) trial.Cardiac, respiratory, and extracorporeal membrane oxygenation–assisted cardiopulmonary resuscitation outcomes (proportions alive at 30 and 90 days for each group)Circuit duration (time to decannulation or time to circuit change) per treatment groupRenal function measured as creatinine and urine output changes during extracorporeal membrane oxygenation (ECMO) per treatment groupRenal replacement treatment on ECMO (type of renal replacement therapy, duration of slow continuous ultrafiltration, type of filter, and duration of filter viability)Incidence of seizures diagnosed during ECMO or up to 48 hours after decannulationTransmembrane oxygenator pressure assessment every 24 hoursOxygenator clot volume as assessed by the extracorporeal life support assessment monitorOxygenator clot volume (by computer tomography imaging)Hemolysis (plasma-free hemoglobin) per treatment groupMean daily heparin dose per kg required to meet target anticoagulation per treatment group

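### Heparin is to be recorded as a 4-hour sustained maximum, from which the listed outcome, a mean daily dose per kg, cannot be derived

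*Protocol article*

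**What the plan says.** The Data Collection section sets one recording rule for continuous treatments and names heparin as an example: "Treatment that is administered continuously (such as heparin or inotropes) will be recorded as maximal values that were maintained for at least 4 hours". It gives no reference period for the maximum (per day or per run). It does not say whether the value is an infusion rate, although that is the natural reading.

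The heparin outcome is the last item of Textbox 3, under Secondary Clinical Outcomes. It is a mean daily dose per kilogram needed to reach the anticoagulation target, by treatment group. The list is titled "Subanalyses for the Nitric Oxide on Extracorporeal Membrane Oxygenation in Neonates and Children (NECTAR) trial", so this is neither a main nor a secondary outcome.

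The same Data Collection section has a general statement that "primary and secondary end points, as well as predetermined physiological variables of interest, will be recorded and entered prospectively". The article does not describe capture of a 24-hour heparin total, a time-weighted rate or boluses.

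On management, the section on concomitant coagulation treatment says: "Methods and goals of anticoagulation will remain unchanged for any other ECMO management and treatments". No heparin rates are given.

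Blood product use is median daily in Textbox 1 (secondary outcomes), "average daily blood product usage" in the text of Secondary Clinical Outcomes, and part of the abstract's outcome summary in the words "as well as total blood product use".

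**The concern.** The recording rule and the outcome are both explicit, and they describe different quantities. The rule keeps the highest level sustained for 4 hours. The outcome needs the whole amount delivered over the day. Hours at lower rates, hours with the infusion off, short peaks and boluses all contribute to the daily dose, and none of them is visible in the sustained maximum. Analysis cannot restore what was not captured.

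The trial is open-label, with anticoagulation left to institutional practice in both arms. Delivered heparin is therefore a natural descriptive check that this co-intervention was similar between arms, and useful background for the clotting and bleeding results. If the arms differ in time at reduced or paused heparin, a sustained maximum can show them as equal. The pilot is also meant to inform a definitive trial, and a mislabelled measure could be carried into it.

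**Working it through.** The plan states no figure to reproduce. The sample size is not an input either: "A sample size of 50 patients has been chosen in line with the recommendations for pilot studies", without reference to heparin. The check is one of definitions, illustrated with hourly rates.

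**Inputs.** The recording rule is from Data Collection and the outcome from Textbox 3. All rates below, in units/kg/h, are assumptions chosen to show the logic. They are not in the article and imply nothing about appropriate dosing. The maximum is taken per day, the reading most favourable to the plan.

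**Formulas.**
- True daily dose = sum of the 24 hourly rates (units/kg/day).
- Recorded value = highest level not undercut for at least 4 consecutive hours.
- Implied daily dose = recorded value × 24.
- Ratio = implied daily dose / true daily dose.

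**Step 1: is the daily dose recoverable?**
- Day A, 4 h at 30 and 20 h at 20: 4 × 30 + 20 × 20 = 520. Recorded: 30.
- Day B, 20 h at 30 and 4 h at 20: 20 × 30 + 4 × 20 = 680. Recorded: 30.

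The true doses differ by 160 units/kg/day and the records are identical. Likewise 24 h at 20 gives 480 and 12 h at 20 with a 12-h pause gives 240, yet both are recorded as 20. One recorded value fits many daily doses, so no conversion exists.

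**Step 2: which way does the error go?**

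| Assumed day | True dose | Recorded × 24 | Ratio |
|---|---|---|---|
| Constant 20 | 480 | 480 | 1.00 |
| 4 h at 30, 20 h at 20 | 520 | 720 | 1.38 |
| 6 h at 30, 12 h at 20, 6 h off | 420 | 720 | 1.71 |
| 4 h at 40, 20 h at 10 | 360 | 960 | 2.67 |
| 3 h at 40, 21 h at 20 | 540 | 480 | 0.89 |
| Alternating 3 h at 10 and 3 h at 30 | 480 | 240 | 0.50 |

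If every rate is held for at least 4 hours and there are no boluses, the recorded value is the day's maximum and cannot lie below the mean. The last two rows break that condition: peaks shorter than 4 hours are dropped and the record falls below the truth. A dropped bolus acts in the same direction. With a constant infusion and no bolus there is no error.

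**Step 3: does the general capture statement close the gap?** It covers primary and secondary end points and unnamed physiological variables. Heparin dose is a treatment and is listed as a subanalysis, so the statement does not clearly reach it, while the specific rule names heparin directly.

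**The case against.** The strongest reply is that this is one of ten items in a list of subanalyses, in a pilot whose analysis is described as exploratory and whose Limitations section says it is not powered for clinical outcomes. No planned analysis conditions on heparin dose. This stands, and it limits the weight of the point.

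A second reply is that the label may mean only the group average of each day's recorded value. The article could be read so, but the quantity would then be an average of sustained maxima, not a dose per day, and the label would still need changing.

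A third is that the full protocol or case report form may capture daily totals. That is possible. However, the point does not rest on silence: the article states a rule, gives heparin as the example, and that rule does not fit the outcome.

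Three stronger readings are tempting and not supported:
- A reader might infer that the recorded data always overstate the dose. They do not: the illustrative ratios run from 0.50 to 2.67 and equal 1.00 for a constant infusion.
- A reader might infer that the clotting, bleeding or coagulation results are compromised. No main or secondary outcome is computed from the heparin record, and the article does not describe heparin pauses or say that nitric oxide would change them. A hidden difference between arms is a possibility, not something the article shows.
- A reader might infer that blood product use is wrongly defined because no weight scaling is stated. That is unit detail an article may leave to the full protocol. Any figure for lost precision would need assumed standard deviations and a log scale, which fails on days without transfusion.

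**Conclusion.** The point holds in a limited form. Following the stated recording rule cannot give the stated heparin outcome, because days with true doses of 520 and 680 units/kg/day can leave the same record. Non-recoverability follows from the definitions. The sizes and ratios rest on assumed rates, on reading the recorded value as an infusion rate, and on a daily maximum. Overstatement is to be expected where rates are held for 4 hours or more, but understatement is possible, so no single direction of bias should be claimed. The consequence is confined to one exploratory subanalysis and any descriptive use made of it.

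The blood product wording is a separate, minor inconsistency: Textbox 1 and the text of Secondary Clinical Outcomes give different summaries, and the two can differ when use is skewed. The abstract's mention of a total is a loose summary and adds little.

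**What to change.** Reconcile Data Collection with Textbox 3 in one of two ways.

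1. **Preferred: keep the outcome and change the capture.** Record total heparin units per 24 h (infusion plus any bolus) together with weight, and report units/kg/day. Scale part ECMO days to 24 h so that the result stays a daily dose per kg. Keep the 4-hour maximum only as a descriptor.
2. **If totals cannot be retrieved: keep the capture and change the label.** Rename the outcome as the maximal sustained heparin value per kg, state the reference period, and do not describe it as a mean daily dose.

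Option 1 costs one extra field on the daily form and some retrospective entry for children already enrolled, assuming that the medication records hold the totals; the article does not say whether they do. Option 2 costs wording only, but gives up the delivered-dose comparison. Neither changes how patients are treated.

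For blood products, choose one summary and use it in both Textbox 1 and the text of Secondary Clinical Outcomes. This is a wording change.
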